### Experimental and control treatment

Clients will receive nine individual 45-minute sessions of therapy for childhood PGD, which are planned to occur once every 1 or 2 weeks. Five 45-minute sessions with one or two of the parents will be planned to be conducted in parallel with these nine sessions. Both treatments will follow the format described by [name] *et al*. [21]. Treatments will be conducted by licensed (post–master’s degree level) therapists.

### Grief-help therapy

Grief-Help therapy for childhood PGD is based on a cognitive-behavioural framework that postulates that symptoms of acute grief persist and exacerbate to the point of impairment in people with PGD [45]. At least three processes influence this: (1) knowledge about the irreversibility of the separation is insufficiently integrated into representational knowledge about the self and the relationship with the lost person, which maintain separation distress and proximity-seeking responses; (2) a propensity to engage in persistent negative thinking about oneself, life and in one’s ability to deal with the pain and grief; and (3) a propensity toward fear and avoidance of external and internal reminders of the loss (termed “anxious avoidance”) and to withdraw from normal routines and valued activities driven by thoughts that one is unable to carry out and/or to enjoy such activities (termed “depressive avoidance”). Alleviation of PGD can be achieved by targeting these processes and using conventional cognitive-behavioural interventions. Imagery exposure (telling the story of the loss event, zooming in on the most painful aspects), *in vivo* exposure (visiting the scene of the death) and confrontational writing (writing a letter to the lost person, explaining what is missed most) are used to promote integration of the irreversibility of the loss with other knowledge. Socratic questioning (that is, identifying and discussing the validity and utility of maladaptive thoughts and altering those) and behavioural experiments (that is, specific assignments to test the validity of cognitions) are used to mitigate maladaptive thinking [46]. Behavioural assignments and skill-training are applied to replace maladaptive coping with more helpful ways of coping; for instance, exposure to avoided stimuli is used to target anxious avoidance, and behavioural activation is employed to interrupt the vicious cycle of depressive avoidance. Cognitive-behavioural Grief-Help therapy includes all these interventions, which are used in a simplified manner in accordance with the developmental level and cognitive abilities of the children.

The treatment is divided into five main parts, all of which are described in a workbook children use throughout treatment. In the first part of treatment (titled “Who died?”), the child is invited to talk about facts of the loss and things she or he misses and wished he or she could still share with the lost person. An important aim of this part is to encourage confrontation with the reality and pain of the loss for the client, as well as for the therapist to gather information about maladaptive thinking and behavioural patterns that are to be addressed later on in treatment. In the second part of the treatment (titled “What is grief?”) a task model (comparable to Worden’s [47] task model of grief) is introduced. The model explains four tasks bereaved children face in coming to terms with loss and the processes that may block achievement of these tasks: Task 1: Facing the reality and pain of the loss; Task 2: Regaining confidence in yourself, other people, life and the future; Task 3: Focusing on your own problems and not only those of others; and Task 4: Continuing activities that you used to enjoy. The task model provides a framework for interventions applied in the next stages of the treatment. For instance, in the third part (“Cognitive Restructuring”) cognitive restructuring is used to work on Task 2. In the fourth part of the treatment (titled “Maladaptive Behaviours”), graded exposure is used to work on Task 1, problem-solving skills are taught to address Task 3 and behavioural activation is used to help achievement of Task 4. In the fifth and final part of treatment (“Moving Forward after Loss”), the skills that are learned during the treatment are reviewed, summarized and written down. Additionally, a plan is discussed for continued practice of learned skills. Specific attention is paid to what the child could do, should his or her emotional problems become exacerbated. Moreover, during the course of treatment, the child writes three letters to an imaginary or real friend as a means by which to facilitate consolidation of the learning process and form a document of learned skills that can be consulted after treatment.

Children receive nine individual sessions. Surviving parents or caregivers receive five parental counselling sessions that are planned in parallel and aimed at supporting them in coaching their child during therapy. Therefore, the emotional problems of the parents are not the specific focus of these sessions.

The therapist reviews the child’s workbook together with the parents during the first two parental counselling sessions. The therapist and parents discuss the grief tasks the child is facing, based on the workbook parts “What is Grief?”, “Cognitive Restructuring” and “Maladaptive Behaviors”. They do this in a general manner but also focus specifically on patterns of behaviour and maladaptive thinking that may block the child’s grieving process.

To promote positive parenting skills and to strengthen the parent–child relationship, parents are given assignments to spend more quality time with their child and to improve communication skills. In sessions 3 and 4, there is a further focus on what parents can do to support their children in their grieving process by helping them to change maladaptive thoughts and behaviours (for example, by helping their children write cognitive diaries, supporting them during their exposure (i.e., to situations, persons and/or memories related to the deceased), solving problems, activating behaviours and providing rewards), and improvement of the parent–child relationship is further discussed. Session 5 is centred on relapse prevention, specifically focusing on signs that could signal to parents that their child might be experiencing new or increased intensity of problems. Parents are then encouraged to make a relapse prevention plan, and attention is again paid to maintaining a good parent–child relationship after the completion of treatment.

### Supportive counselling

Supportive counselling for childhood PGD is based on nondirective treatments for bereaved children [48,49] and adults [44,50] and on treatments for children with PTSD [51]. As a rationale for supportive counselling, it is explained to children that PGD coincides mostly with various emotional, social and practical difficulties and that discussing these could bring relief from the emotional burden of bereavement. Children are encouraged to express all their feelings and thoughts about the loss. The rationale for this encouragement of children to express their feelings is that bereaved children can experience many intense and different feelings and thoughts about the loss and that they can learn to cope with those feelings by expressing them. Expressing feelings of grief can take the form of talking, playing or making a memory box or book. Therapists are unconditionally supportive of issues children bring up and their attempts at problem-solving. They do not address cognitions and give no instructions for exposure.

As in Grief-Help therapy, supportive counselling includes nine individual sessions with the child and five counselling sessions with the parents or other caregivers. The treatment is divided into three parts. The first sessions are devoted to identifying difficulties children experience in their everyday lives. Children are encouraged to express all their feelings and thoughts about the loss in any way they like. As a second step, the therapist and child review all themes that have been identified in the first phase of therapy in more detail. The child decides if she or he prefers to talk, play or express their feelings in any other possible way. In the last phase, the therapist and child speak about or play saying goodbye to each other.

Counselling sessions with parents are planned every 2 weeks. In the first session, a plan is made about which themes parents want to discuss and in which order they should be talked about. The therapist helps the parents to think about solutions to problems that they encounter in supporting their child. The therapist can also suggest themes. Examples include (1) the grieving process; that is, What does the parent think about the grieving process, how do parents support their child, what are the main problems for the child? (2) feelings and thoughts the child expresses about the loss and the reactions of the parents to these expressions; (3) coping behaviours of the child related to the loss; that is In what ways does the child cope with his or her feelings and thoughts? What do parents think helps the child and what does not? and (4) the development of the child in the near future; that is, What are potential problems, given the loss and the development of the child thus far? How do the parents cope with those ideas about the future of the child? There are no homework assignments for children and parents in the supportive counselling sessions.

### Statistical analyses

Most analyses will be conducted using the software program SPSS (SPSS, Inc, Chicago, IL, USA). Descriptive analyses will be carried out using standard methods. For analysis of the primary and secondary outcome measures, we will use analysis of covariance with the outcome measures posttreatment or at follow-up sessions as dependent variables, treatment condition as a factor and preintervention scores of the outcome variables as covariates. We will compare the scores of children in both groups with their own scores on previous assessments by using regression analysis and/or structural equation modelling. Mediator and moderator models will be tested. Analysis and reporting of the results will be carried out according to the CONsolidated Standards of Reporting Trials (CONSORT) 2010 Statement guidelines [52].

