### Sample size

Our sample size calculation is based on the conventional significance (α) and power (1 – β) levels of 0.05 and 0.80, respectively, planning one-sided testing. The sample size of this study is based on the expected difference on the primary outcome variable (that is, PGD symptoms) between the two conditions. On the basis of a power of 0.80, an α of 0.05 and an expected dropout percentage of 20%, we will need 80 participants for each condition to show an effect size of 0.50 [44]. Therefore, we have determined the total sample size to be 160.

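### Visit-by-visit ANCOVA ignores intermediate scores of children lost later; a mixed model over A2-A5 would reduce bias at the follow-up visits if data are missing at random

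*Protocol article*

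**What the plan says.** The Statistical analyses section sets the model for the primary outcome (IPG-C) and the secondary outcomes: "we will use analysis of covariance with the outcome measures posttreatment or at follow-up sessions as dependent variables". Treatment condition is the factor and the baseline score of the same outcome is the covariate. The section then adds: "We will compare the scores of children in both groups with their own scores on previous assessments", by regression and/or structural equation modelling, and says that mediator and moderator models will be tested.

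Three other places bear on this:
- Trial objective: the hypothesis is that Grief-Help does better than supportive counselling right after treatment and at each of the three follow-ups.
- Procedure and randomisation, and Table 1: the IPG-C and all secondary outcomes are collected at A1 (baseline), A2 (after treatment) and A3, A4 and A5 (3, 6 and 12 months later).
- Sample size: the calculation reckons with "an expected dropout percentage of 20" per cent and concludes "we will need 80 participants for each condition to show an effect size of 0.50".

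**The concern.** An ANCOVA of the A5 score on arm and baseline has no place for the A2, A3 and A4 scores. A child who supplies those and then leaves contributes nothing to the A5 comparison unless the A5 score is imputed. Raising the sample size for dropout replaces lost numbers, but it does not protect against selective loss.

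Selective loss that differs by arm is plausible from the article's own description. Grief-Help uses imaginal and in vivo exposure and behavioural assignments. Supportive counselling gives no exposure instructions and no homework. If children leave according to how they were doing at earlier assessments, and do so differently by arm, those still present at A5 are no longer comparable given baseline alone. At stake is the accuracy of the claims at 3, 6 and 12 months.

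The comparisons with own earlier scores raise a second, smaller matter. Among children who enter because they seek help for grief symptoms, change over time mixes treatment with natural recovery and regression to the mean.

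**Working it through.** **1. The plan's own figure.** Inputs from the Sample size section: effect 0.50 SD, α 0.05, power 0.80, dropout 20%.
- Two-sided, normal formula: n = 2 × (1.960 + 0.842)² / 0.50² = 62.8, so 63 per arm; 63 / 0.80 = 78.75, so 79.
- Two-sided t-test: 63.8, so 64 per arm; 64 / 0.80 = 80. This reproduces the planned 80.
- With 80 × 0.80 = 64 children left per arm, two-sided power is 0.81 without any gain from the covariate.

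The loss of numbers is therefore already paid for, and what remains is bias. (The section also says "planning one-sided testing". Those inputs give 50 or 51 evaluable, hence 63 or 64 per arm after dropout. That mismatch is a separate matter.)

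**2. When the per-visit ANCOVA is biased.** The model at visit k is Y_k = a + τ·arm + b·Y_1 + e, fitted to children with Y_k observed. If loss depends only on arm and Y_1, the estimate of τ is unbiased. If loss also depends on intermediate scores, the mean of e among those observed can differ by arm, and that difference enters the estimate. A likelihood model over A2-A5 conditions on the intermediate scores and so corrects for loss that depends on them.

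**3. Size.** The article gives no correlations between assessments and no dropout timing or mechanism, so these are assumptions: SD 1, correlation between adjacent assessments 0.5 or 0.7 falling by 0.04 per further step, 80 per arm, true effect −0.50 SD at every visit, 4,000 simulated trials per scenario. Except in the first two rows, dropout is monotone and spread over A2-A5. The mixed-model estimate comes from successive regressions of each visit on arm and all earlier scores. Simulation error of a mean is about 0.17 / √4000 = 0.003. Estimates at A5, for correlation 0.5 / 0.7:

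| Assumed dropout | Missing at A5 | ANCOVA | Mixed model |
|---|---|---|---|
| All before A2, at random | 20% | −0.498 / −0.505 | −0.498 / −0.505 |
| All before A2, depending on baseline | 22% | −0.505 / −0.502 | −0.505 / −0.502 |
| Spread over visits, at random | 20% | −0.500 / −0.500 | −0.500 / −0.500 |
| On previous score, same rule in both arms | 23% / 22% | −0.477 / −0.482 | −0.495 / −0.499 |
| On previous score, opposite direction by arm | 18% | −0.421 / −0.421 | −0.502 / −0.498 |
| On the current, unseen score, opposite by arm | 18% | −0.344 / −0.363 | −0.379 / −0.406 |

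- Loss depending on the previous observed score: ANCOVA bias is 0.50 − 0.48 = 0.02 SD (same rule) to 0.50 − 0.42 = 0.08 SD (opposed rule). That is 0.02 / 0.50 = 4% to 0.08 / 0.50 = 16% of the target. The mixed model removes it.
- Loss depending on the unseen score: the mixed model is closer but still off by 0.50 − 0.38 = 0.12 SD or 0.50 − 0.41 = 0.09 SD.
- At A2 the two estimates agree in every scenario, including the last, where both are biased (−0.424 / −0.448).
- Standard errors are practically equal, for example 0.164 against 0.162 at A5 with random loss and correlation 0.5.

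**4. Direction.** A second set of assumptions had correlation 0.45 + 0.55 × 0.5^lag, dropout only after A2, and loss depending on the A2 score more steeply in Grief-Help (3,000 trials per scenario). With a true effect of 0.50 and 21% missing, ANCOVA gave 0.54 and the likelihood estimate 0.50. With a true effect of 0 and 27% missing, ANCOVA gave 0.06 in favour of Grief-Help and the likelihood estimate 0.00. Here the bias flatters Grief-Help; in the table it shrinks the effect.

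**The case against.** Baseline-adjusted ANCOVA is a standard, valid method, and the case against this point has real weight.

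- **A reader might infer that the plan drops every child with a missing assessment.** The article does not say so. It names no analysis set and no missing-data rule, and imputation followed by ANCOVA would fit its wording. A full protocol or analysis plan may settle this, so the silence is not a fault. What stands is that the stated outcome model itself has no place for the intermediate scores.
- **A reader might infer that a mixed model removes the bias for all randomised children.** It does not. It corrects only for loss that depends on observed data, under a correctly specified model. Children with no post-baseline score add nothing to the contrast, and under monotone dropout the A2 estimate is the same as from ANCOVA.
- **The size is modest and assumed.** The second set's bias of 0.04 to 0.06 SD compares with a standard deviation of the estimate of about 0.16, and its null scenario has more missing data than the planned 20%. This limits the weight of the point but does not cancel it.
- **A reader might infer that change from children's own earlier scores will serve as proof of effectiveness.** The article does not state that. It gives the outcome analysis to the between-arm ANCOVA, its hypothesis is between groups, and the sentence stands directly before the mediator and moderator models. Structural equation modelling, which can use incomplete records, is also named there. Only a request for clear labelling survives.

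**Conclusion.** The point holds as a criticism of a stated method. The outcome model uses one post-baseline score at a time in a trial that collects four, hypothesises an effect at all four and expects 20% dropout. Unless scores are imputed, the A3-A5 tests rest on children present at that visit and ignore what is known about those who left.

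Where dropout depends on earlier observed scores, the A5 estimate is biased by roughly 0.02 to 0.08 SD, with the larger values when the dependence differs by arm. The sign is not known beforehand. The range rests on assumed correlations and dropout mechanisms. If loss is random, or depends only on arm and baseline, the planned ANCOVA is already unbiased. A mixed model was no worse in bias, and practically equal in standard error, in every scenario tried. The change is worth making because it is cheap and helps at the follow-up visits; the point does not invalidate the trial.

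**What to change.** Analyse the IPG-C and each secondary outcome with one likelihood-based linear mixed model for repeated measures over A2-A5, with unstructured covariance and arm-by-time and baseline-by-time terms. Include all children with at least one post-baseline score, in the arm to which they were randomised, and take the between-arm contrast at each visit from this model. Keep the per-visit ANCOVA as a sensitivity analysis, and add a sensitivity analysis for data missing not at random. State that comparisons with children's own earlier scores are descriptive or serve the study of mechanisms, and rest every statement of effectiveness on the between-arm contrast.

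The cost is a change of wording in the analysis plan. SPSS, the program already named, can fit the model. The planned 160 children and the assessment schedule stay as they are. The price is reliance on the missing-at-random assumption and on a covariance structure, which the sensitivity analyses are there to probe.

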### Participants

Participants will be bereaved children and adolescents (and their parents) who apply for help in outpatient mental health care clinics in The Netherlands. The following inclusion criteria will be used: (1) ages 8 through 18 years, (2) loss of a close relative, (3) symptoms of PGD as the primary problem and reason for seeking therapy, (4) absence of mental retardation, (5) absence of severe conduct disorder and developmental disorders, (6) no concurrent psychological or psychopharmacological treatment and (7) no current substance abuse or dependence, no psychotic symptoms and no severe depression with risk of suicide in participating children or their parents.

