### Procedure and randomisation

Potentially eligible participants (and their parents) referred to the participating clinics by their general practitioners will receive oral and written information about the research program. Surviving parents’ consent will be obtained for their children to participate. Assent or consent will be obtained from the children, depending on their age. Children will then complete baseline measures (assessment 1 (A1)) in the presence of a therapist. Parents will also complete baseline measures at A1.

Randomisation will take place after informed consent is obtained and after completion of the baseline measures (A1). Participants will be randomly allocated to one of two treatment conditions. Both treatments will be introduced to participants as potentially useful interventions for bereaved children. Four follow-up assessments will be conducted: directly after completion of the treatment (A2) and three, six and twelve months later (A3, A4 and A5, respectively).

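### The outcome model and the sample size treat children as independent although therapists at several sites deliver both treatments; if therapists work in one arm only, standard errors will be too small

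*Protocol article*

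**What the plan says.** All references are to the Protocol article.

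- *Statistical analyses* fixes the model for primary and secondary outcomes: ANCOVA of the post-treatment or follow-up score, with "treatment condition as a factor and preintervention scores of the outcome variables as covariates". It names no therapist or clinic term.
- *Sample size* uses "levels of 0.05 and 0.80, respectively, planning one-sided testing", "an expected dropout percentage of 20" per cent, and concludes that "we will need 80 participants for each condition to show an effect size of 0.50". No intraclass correlation or design effect enters.
- *Experimental and control treatment*: "Treatments will be conducted by licensed" therapists, with nine individual child sessions and five parent sessions. *Participants* recruits children "who apply for help in outpatient mental health care clinics in The Netherlands", and *Trial status* refers to therapists trained at different sites. The number of therapists, their caseload, and whether one therapist treats in both arms are not given.
- *Procedure and randomisation*: "Participants will be randomly allocated to one of two treatment conditions". Allocation is described at the level of the participant.

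**The concern.** In individually delivered psychotherapy the therapist is part of what is being compared. Children of one therapist share that therapist's skill and style, and often the clinic's case mix, so their outcomes may be correlated. A model with only condition and baseline score attributes none of the variation to therapists.

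What follows depends on delivery. If each therapist works in one arm, differences between therapists are part of the difference between arms. The ordinary ANCOVA standard error leaves that variance out, so the test rejects too often and the intervals are too short. The sample size, built on independent observations, then also has less information than it counts on. If each therapist works in both arms, the common therapist effect largely drops out of the comparison. What can remain is variation between therapists in the treatment effect itself.

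**Working it through.** **Step 1. Reproduce the plan's figure.** Inputs from *Sample size*: d = 0.50, α = 0.05, power 0.80, dropout 20%. Formula: n per arm = 2(z_α + z_β)²/d².

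- Two-sided: 2(1.960 + 0.842)²/0.25 = 62.8, so 63 (64 by t-test). Divided by 0.8: 79 (80 by t-test).
- One-sided: 2(1.645 + 0.842)²/0.25 = 49.5, so 50 (51 by t-test). Divided by 0.8: 63 (64 by t-test).

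The 80 per arm is reproduced by the two-sided formula for independent observations, so it contains no allowance for clustering on that basis. The text says one-sided. That mismatch is a separate matter, but it decides how much slack there is, so both versions are carried below.

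**Step 2. Slack in the design.** Completers per arm: 80 × 0.8 = 64. Power without clustering is 0.81 two-sided and 0.88 one-sided. The design effect that brings power down to 0.80 is 64/62.8 = 1.02 two-sided and 64/49.5 = 1.29 one-sided.

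**Step 3. Therapists nested in arms.** The documents give neither ICC nor caseload. Assumed: ICC 0.02–0.10 and m = 3–8 completers per therapist. Formulas:

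- design effect DE = 1 + (m − 1) × ICC
- effective n per arm = 64/DE
- actual type I error when clustering is ignored: 2[1 − Φ(1.960/√DE)] two-sided, 1 − Φ(1.645/√DE) one-sided
- power: normal approximation at d = 0.5 with the effective n, that is, with the correct standard error

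| m | ICC | DE | Effective n | Type I, two-sided | Type I, one-sided | Power, two-sided | Power, one-sided |
|---|---|---|---|---|---|---|---|
| 3 | 0.02 | 1.04 | 61.5 | 5.5% | 5.3% | 79% | 87% |
| 5 | 0.02 | 1.08 | 59.3 | 5.9% | 5.7% | 78% | 86% |
| 5 | 0.05 | 1.20 | 53.3 | 7.4% | 6.7% | 73% | 83% |
| 5 | 0.10 | 1.40 | 45.7 | 9.8% | 8.2% | 67% | 77% |
| 8 | 0.05 | 1.35 | 47.4 | 9.2% | 7.8% | 68% | 79% |
| 8 | 0.10 | 1.70 | 37.6 | 13.3% | 10.4% | 58% | 70% |

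The t-test version of the last row gives 57% and 69%.

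**Step 4. Therapists crossed with arms.** The DE formula of step 3 does not apply. A therapist effect common to both arms cancels in the comparison, so leaving it out need not make the test too liberal, and including it removes noise.

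**The case against.** **The harm is conditional.** Every figure in step 3 covers the nested case, with an assumed ICC and caseload. A reader might infer that the planned test is known to be too liberal. The article does not support that, because it does not say which delivery structure applies. This limits the claim, but it is also why the structure should be stated.

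**Power may still be adequate.** A reader might infer that the 80% power is not delivered. Under the stated one-sided test that is not so in the middle case (ICC 0.05, five children per therapist), where power is about 83%. The step 3 figures also omit the precision gained from baseline adjustment. With an assumed baseline–outcome correlation of 0.4–0.5, which the article does not give, two-sided power at DE 1.20 returns to about 80–85%; with 0.3 it is about 77%. This objection stands for power. It does not remove the type I error inflation in the nested case.

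**This is detail for the analysis plan.** Random-effect structure and degrees of freedom often belong there. But the article states the model's terms, and an analysis plan that follows the sentence literally would omit therapists.

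**Siblings.** A reader might also infer that siblings enter separately, that this too makes errors too small, and that parents may attend both programmes, since "Surviving parents or caregivers receive five parental counselling sessions that are planned in parallel" with the child's sessions and both arms have such sessions. The article does not show that siblings are enrolled or split between arms, and a family rule may sit in the full protocol. Nor do the two harms occur in the same sibling pair. Parents meet both programmes only if siblings are in different arms, and ignoring the pairing there makes the standard error too large. Errors are too small only if siblings share an arm. Simulating separate randomisation of sibling pairs (128 completers, 20–40% of children in pairs, sibling ICC 0.5) gave two-sided type I error of 0.049–0.050. No error is claimed on this point.

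**Conclusion.** The concern holds in a limited form. The stated ANCOVA and the stated sample size both assume independent children, while the article itself describes individual treatment by several therapists at several sites.

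For nested therapists, under the assumed ICC and caseload, two-sided type I error rises from 5% to between about 5.5% and 13% (one-sided to between about 5.3% and 10%). Whether power falls below 80% depends on sidedness. A design effect of about 1.02 is enough if testing is two-sided, and about 1.29 is needed if it is one-sided as written, in both cases before any gain from baseline adjustment. For crossed therapists the consequence is mainly lost precision, apart from any variation between therapists in the treatment effect.

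The change is worth making because the same therapist term serves both cases and costs little. The article does not support saying that the trial is underpowered or that its type I error is inflated as a matter of fact.

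**What to change.** - State whether therapists treat in one arm or both, and record a coded therapist and clinic identifier for every child in the data set. *Protection of data privacy* has the key lists deleted after the final analyses, so this must be done before then.
- Add to the ANCOVA a therapist random effect, nested in or crossed with arm as delivery actually was, and a clinic term, with small-sample degrees of freedom.
- State beside the sample size that 80% power assumes no therapist clustering, and give the range from step 3 for the sidedness actually used.
- If siblings from one family are enrolled, record a family identifier and include a family effect.

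Cost: one or two identifier variables and a few lines of analysis text. The sample size and the allocation procedure do not change. Downside: slightly wider intervals if therapists are nested in arms.
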